**Figure 2: Phase 2 trial schematic.**

### Case definition and patient enrolment:

Patients will be drawn from the communities where the CHWs operate and the clinics which supervise and support those CHWs. Inclusion criteria will be:

- Any patient where the CHW* or clinician considers malaria in the diagnosis – either prescribing an antimalarial or would request a malaria test if available or referring for diagnosis of malaria elsewhere.
- Patient, or parent/guardian, gives informed consent to the study.

*any community health worker who consults with patients and prescribes treatment, and is administratively attached to one of the study clinics.

Exclusion criteria will be

- Patients with a diagnostic result from another facility.
- Patients referred on for diagnosis in the private sector.
- Patients who have signs of severe or complicated disease and are referred prior to giving any diagnosis using the interventions.

Patients can be enrolled during any consultation with a CHW no matter where it takes place. The consultation could be made at the health post, the patient’s residence, or even outside in the street or fields. The CHW will also use the standard national HMIS tool for recording all their consultations, which will also allow assessment of any changes to practice within the community by identifying changes in the number of each type of consultation (for example, community DOTS, health awareness, condom distribution, etc).

If the patient gives informed consent, the CHW will assign a unique patient number and note the patients information on a pro-forma pictorial record form (Patient Tracking Form, see section 2.6). The patient tracking form has been designed for semi literate and illiterate health workers and has been pretested and validation in field testing using CHWs in Nangahar province.

Patients will also be recruited in clinics during the study at clinic level. Those who present without visiting a CHW (i.e. have not been enrolled at community level and self refer) will be enrolled according to the inclusion and exclusion criteria. Patients who present at the clinic who have been enrolled at community level will also be enrolled if they present to the clinic and these will be linked to the consultation at community level though the use of the patient ID card - All patients enrolled at community level will be given a study patient ID card which will identify them as having been enrolled by a CHW and note their patient number from the community level enrolment.

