While the rollout of RDTs at clinic level has some evidence base (in part, from the previous ACTc studies), there is little available data on the effectiveness with which this intervention can be provided at community level through CHWs. The data that does exist locally is based on two studies, one conducted in 2006^[[1]](#footnote-1)^ and one ongoing pilot programme^[[2]](#footnote-2)^. Evidence from the study and from the pilot programme suggests that RDTs are not utilised effectively by CHWs. In the study, high rates of invalid tests were reported due to user error, and in both programmes, RDTs are incorrectly applied to patient’s symptoms. The results are that very large numbers of RDTs are used, and very few cases of malaria are adequately detected. The effect of RDTs on treatment decisions and accuracy was not noted by either study.

Use of RDTs at community level will also have an effect on current guidelines for management of febrile illness and diseases of children. The current community IMCI guidelines for Afghanistan (and most of Asia) do not include RDTs in the differential diagnosis of childhood diseases in the community. The current guidelines favour a blanket approach to treatment of “suspected malaria” where there is no other obvious cause of illness and the patient is in an endemic area. Changing these guidelines requires an evidence based approach to assess both the clinical and economic aspects of the intervention – something which has thus far not been conducted despite the trend in programming which has now started to deploy RDTs much more widely.

This study aims to provide evidence on the effectiveness of RDTs that have been deployed at community level by measuring the accuracy of the tests themselves, and the accuracy with which treatment is provided to malaria positive and malaria negative cases.

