### Balance criteria:

The following variables that are expected to be important correlates of the primary outcome and on which we wish to achieve balance were based on a data collected in 2009 in the same study clusters and over the same study period i.e. July to December.

1. Harmonic mean. For a given number of clusters and overall sample size maximum statistical efficiency is obtained if an equal number of patients per cluster are selected. The total sample size of 1500 across 22 clusters would require an *arithmetic* mean of 68 patients per cluster. However, due to the huge variability in the proportion of patients seen with suspected diarrhoea, URTI and malaria (when CHWs are likely to use RDTs) per cluster this approach was not seen as appropriate for several reasons including time to reach sample size quota, and cluster representation. Hence the sample size was weighted according to the cluster proportion of patients seen with suspected diarrhoea, URTI and malaria to achieve a *harmonic* mean of 68 patients per cluster in each arm. Since the sample size calculation was done before randomisation the overall harmonic mean (for all clusters) was used but this does not guarantee a harmonic mean of 68 per arm and therefore this was included as a restriction factor in the randomisation.
2. Total sample size. The precision and power of a study are usually maximised when sample sizes are similar in the treatment arms. In CRTs this means that the number of clusters as well as the number of individuals should be similar across treatment arms. Therefore, due to the variability in sample size per cluster this was also added as a restriction factor.
3. Number of health posts. There is a substantial amount of variation in the number of health posts per cluster from 2 to 26. Clusters (clinics) with bigger catchment populations have more health posts and therefore by balancing on this factor and equal sample size per arm will be achieved.

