### Trial Primary Outcome:

The primary outcome of the study is:

- Proportion of patients (in)correctly treated by CHWs.

Correct treatment is defined as:

- - Treatment of PCR confirmed Pf with SP/AS.
  - Treatment of PCR confirmed Pv with CQ (regardless of accompaniment with SP or addition of primaquine).
  - No antimalarial for PCR confirmed negative diagnosis.

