## Sample Size and Statistical Methods:

### Sample Size Assumptions:

Key parameters and assumptions used to calculate the sample size are listed below:

- Number of clusters (clinics): 22
- Number of Health Posts: 207
- Number of CHWs: 414
- Expected difference in primary outcome in Phase 1 (40%):
  - Arm 1 - Non-intervention: 10% correctly treated vs.*
  - Arm 2 – RDT: 50% correctly treated*
- Expected difference in major secondary outcome (in phase 1):
  - Proportion of Pf positive patients receiving ACT: 0.5% in arm 1 vs. 50% in arm 2.*
  - Proportion of malaria negative patients treated with antimalarial: 90% in arm 1 vs. 50% in arm 2*
  - Proportion of malaria negative patients treated with antibiotic: 5% in non-intervention arm, 15% in RDT arm.
- Expected difference in primary outcome in Phase 2 (20%):
  - Arm 2 – RDT: 50% correctly treated.
  - Arm 3 – RDT extended programme: 70% or greater are correctly treated.
- Expected differences in major secondary outcome (in phase 2):
  - Proportion of Pf positive patients receiving ACT: 50% in arm 2 vs. 85% in arm 3.
  - Proportion of malaria negative patients treated with anti-malarial: 50% in RDT arm, 25% in RDT extended programme arm.
  - Proportion of malaria negative patients treated with antibiotic: 15 % in RDT arm, 20% in RDT extended arm.
- Sub-group analysis assumes that 40% of patients are under 10yrs*.

* estimates are based on initial results from the current randomised trial, based on data from 22 clinics in Afghanistan. There are no estimates in this region for effectiveness at CHW level.

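### Phase 1 entry rests on the CHW's own test, prescribing or referral decision, so Arm 2 risks enrolling more untreated malaria-negative patients and scoring higher with no change in prescribing

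*Protocol*

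**What the plan says.** Section 2.5.7 admits any consenting patient in whom the CHW or clinician considers malaria, shown by "either prescribing an antimalarial or would request a malaria test if available or referring for diagnosis of malaria elsewhere". The wording is the same for every arm, and section 3.3 gives all CHWs the same training in enrolment.

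Under section 2.5.1, Arm 1 CHWs work by clinical diagnosis and referral without RDTs. Arm 2 CHWs hold RDTs and are taught a revised IMCI algorithm with an RDT in the fever pathway.

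Section 2.5.3 weights the clinic quotas by the "proportion of patients seen with suspected diarrhoea, URTI and malaria (when CHWs are likely to use RDTs) per cluster". On earlier local use of RDTs by CHWs, section 1.2 reports: "The results are that very large numbers of RDTs are used, and very few cases of malaria are adequately detected".

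The primary outcome in section 2.6.1 is "Proportion of patients (in)correctly treated by CHWs", and one of the ways to be correct is "No antimalarial for PCR confirmed negative diagnosis". Section 2.8.1 plans on "Arm 1 - Non-intervention: 10% correctly treated vs" 50% in Arm 2. It also assumes that 90% (Arm 1) and 50% (Arm 2) of malaria-negative patients receive an antimalarial.

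**The concern.** Each entry trigger is a decision made after allocation by a CHW who knows the arm, and each is a decision the intervention is meant to change. Randomising clinics does not protect against selection of patients that happens later, inside the clinics' health posts.

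The test trigger works differently in the two Phase 1 arms. In Arm 2 it is an event: an RDT was used. In Arm 1 it is what the CHW says would have been done, which leaves no trace. Section 1.2 adds that current guidelines point to suspected malaria where no other cause is obvious. A patient with a cough or diarrhoea is therefore less likely to be thought of as a malaria suspect in Arm 1 than to be tested in Arm 2.

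The scoring turns this into bias in one direction. A PCR-negative patient who is tested and given no antimalarial counts as correct. A PCR-negative patient who enters because an antimalarial was prescribed counts as incorrect by definition. If Arm 2 brings in more of the first kind, its score rises even though no patient is treated differently. The primary result would then mix case mix with any real change in prescribing.

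**Working it through.** **Inputs.** Planned Phase 1 rates are 10% and 50% (2.8.1). CHW treatments in the 22 clinics, July to September 2010 (2.8.2): malaria 2,518, URTI 6,429, diarrhoea 6,772. Clinic quotas are in 2.8.3 and the allocation in 2.5.5.

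**The plan's own figure.** 50% − 10% = 40 points. The malaria-negative assumptions give the same rates when most patients are negative: 1 − 0.90 = 10% and 1 − 0.50 = 50%.

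**Model with no change in treatment.** Core patients enter in both arms, are treated alike and are 10% correct. For each core patient there are *k* further patients whom Arm 2 tests and enrols. They are PCR-negative and would get no antimalarial in either arm. Arm 1 captures a fraction *r* of them.

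- Arm 2 score = (0.10 + k)/(1 + k)
- Arm 1 score = (0.10 + rk)/(1 + rk)

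With k = 0.8, Arm 2 scores 0.9/1.8 = 50%, the planned Arm 2 rate. The extras are then 0.8/1.8 = 44% of Arm 2 enrolment.

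| Arm 1 capture r | Arm 1 score | Spurious difference |
| --- | --- | --- |
| 0 | 0.1/1.0 = 10.0% | 40.0 points |
| 25% | 0.3/1.2 = 25.0% | 25.0 points |
| 50% | 0.5/1.4 = 35.7% | 14.3 points |
| 75% | 0.7/1.6 = 43.8% | 6.2 points |
| 100% | 0.9/1.8 = 50.0% | 0 |

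**Are there enough such patients?** URTI and diarrhoea treatments total 6,429 + 6,772 = 13,201, or 13,201/2,518 = 5.2 per malaria treatment. Reaching k = 0.8 takes 0.8 × 2,518/13,201 = 15.3% of them. In Nangarhar alone it takes 0.8 × 2,471/7,347 = 26.9%. Treatments given stand in for consultations here.

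**If some extras are PCR-positive.** Let a share q be positive; untreated, they score as incorrect. With r = 0, reaching 50% then needs k = 0.40/(0.50 − q). The documents give no q, so I show an assumed range:

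- q = 5%: k = 0.89, or 17.0% of the URTI and diarrhoea treatments
- q = 10%: k = 1.00, or 19.1%
- q = 20%: k = 1.33, or 25.4%

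**Kunduz.** The five Arm 1 clinics there have quotas of 124 + 276 + 25 + 112 + 107 = 644 patients, against 3 + 3 + 2 + 6 + 4 = 18 malaria treatments in three months. Arm 2 has 520 against 29. If the Arm 1 quotas are to be met, nearly all entry must come through referral or the hypothetical-test clause.

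**Phase 2.** Both arms hold RDTs, so the difference in trigger is smaller. Arm 3 training could still change whom CHWs test. By the same formula, turning 50% into 70% would need k = (0.70 − 0.50)/(1 − 0.70) = 0.67.

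**The case against.** The strongest reply is that the hypothetical-test clause is there to make the arms alike. It makes an untested, untreated Arm 1 patient eligible, and all CHWs get the same enrolment training. The planning figures agree that such patients are expected: if 90% of Arm 1 negatives get an antimalarial, 10% do not. The quotas of both arms also use the same malaria, URTI and diarrhoea counts. This stands. If Arm 1 CHWs applied the clause exactly as Arm 2 CHWs use RDTs, r would be 100% and the bias would vanish. But nothing in the protocol lets anyone verify that they do. Similar arm totals (1,280 and 1,262 in Table 4 of 2.5.5) would not reveal a different case mix, because the quotas fix them.

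The HMIS tool, and the secondary outcome on CHW attendances, would allow a check on enrolment. Neither is used to define who is eligible.

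Three stronger readings are tempting and not supported:

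- A reader might infer that untreated URTI and diarrhoea patients never enter Arm 1, or that Arm 1 enrols only antimalarial recipients. The eligibility text and the 90% assumption both contradict this.
- A reader might put every URTI and diarrhoea patient into Arm 2, giving (0.1 × 2,518 + 13,201)/15,719 = 86%. That is an upper bound. It needs universal testing, while Arm 2 training places the RDT in the fever pathway.
- A reader might infer that the exclusion "Patients referred on for diagnosis in the private sector" falls mainly on the arm without a test. The documents give no such referral rates, and Arm 1 practice is referral to a clinic.

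**Conclusion.** The point holds for Phase 1 as a risk built into the entry rule, not as a certainty. Its direction is clear: more untreated negatives in Arm 2 raise that arm's score. Its size depends on how many of the extra patients Arm 1 captures, which the documents do not give. In the illustration it runs from 40 points with no capture to 6 points at 75% capture and zero at full capture.

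These figures assume a core group that is 10% correct in both arms, 0.8 extras per core patient, and extras who are all PCR-negative and untreated. Section 2.8.1 itself says that no estimates exist for CHWs in this region and that the 10% comes from the clinic-level trial. The illustration therefore shows what the rule permits; it does not forecast the result. Phase 2 is less exposed.

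This should be settled in the enrolment rule, because later adjustment cannot recover Arm 1 patients who were never enrolled and so have no PCR result.

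**What to change.** For the primary comparison, replace the decision-based trigger in 2.5.7 with one symptom-based entry rule, identical in all arms, for example fever or a history of fever. The CHW should record it on the form before any test or treatment decision. Keep patients who are tested or treated without fever as a separately reported set, so that misuse of RDTs stays visible. Report enrolled patients per HMIS consultation, by type and arm, as a check on differential enrolment.

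The work is modest. It means amending the eligibility text, the CHW recruitment SOP and the common enrolment training. The form already records fever (2.7.2), blood spots are already taken in the non-intervention arm (2.9.2), and the secondary objectives already concern patients presenting with fever (2.1).

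There are three downsides:

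- Some Arm 1 patients not suspected of malaria would give a blood spot. The statement in 2.10.3 that most samples would be taken anyway would need revising.
- The observed effect may be smaller than 10% against 50%.
- Fever would still be recorded by a CHW who knows the arm, so the rule reduces the bias without removing it. The HMIS comparison is needed for that reason.

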### Trial Arms:

**Phase I:**

*Arm 1: Non-intervention arm:*

The non-intervention arm will be based on the existing clinical diagnosis, pre-referral treatment and referral to a clinic in areas where RDTs have not been deployed at CHW level. Arm 1 CHWs will receive refresher training according to the National Strategy for CBMM which includes the current IMCI guidelines.

Vs:

*Arm 2: RDT Arm*

Provision of community level diagnostics by rolling out RDTs to CHWs through the national strategy for Community based Management of Malaria. The arm has been designed exactly as the current National guidelines for RDT implementation..The arm will include:

- Clinic level microscopy or RDT and CHWs using RDTs to provide parasitological diagnosis to diagnose, treat and/or refer patients. Under this scheme, CHWs will be provided with CQ, SP and artesunate (AS). Depending on the diagnostic result, they prescribe according to the National Treatment Guidelines (CQ for confirmed vivax, SP and AS for confirmed falciparum, and no antimalarial for a negative result).
- CHW training will be conducted exactly as described in the CBMM strategy, using a “trickle down approach” where Training of Trainers takes place at the central level for provincial trainers of local NGOS who run the health service. These, in turn, run workshops for training CHSs and CHWs (see section 2.2 for pre-evaluation of training and roll-out). Participants will receive training to enforce revised IMCI guidelines, taken from the CBMM strategy document, which include an RDT in the algorithm for fever (see annex 2).
- There are no plans for additional support or refresher training, and no plans for quality control and assurance contained in the National Plan.
- CHWs are not equipped with suitable storage facilities for the RDTs, for example evaporative coolers.
- Monitoring and evaluation takes place according to the draft strategy.

The second phase of the trial will be initiated in Feb 2012. The second phase of the trial will re-randomise clinics to either the RDT arm (as in arm 2, above) and a third arm (arm 3). The third arm will answer the question: “how can the performance of RDTs at community level be enhanced?”. The same set of outcomes will be used to measure the relative effectiveness of each approach. A revised random allocation using the same methods will be conducted for the Phase II randomisation.

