### Sample Collection:

Filter paper blood spots will be collected from participants. These will be collected using clean disposable lancets and gloves at the same time as the RDT is used. If the RDT is not used (i.e. in the non-intervention group) then the filter paper will be collected during the consultation. Filter papers will be stored in ziplock bags with silica beads. They will be returned to the clinic within 7 days and stored in a refrigerator (4^o^C) until shipped to Kabul for evaluation (see 2.8.4, below)

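### The private-sector referral exclusion removes patients for a CHW decision made after randomisation, is likely to act differently by arm, and can bias the Phase I primary outcome in a direction the protocol does not settle

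*Protocol*

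**What the plan says.** Section 2.5.7 (Case definition and patient enrolment) includes any patient in whom the CHW or clinician considers malaria, shown by "either prescribing an antimalarial or would request a malaria test if available or referring for diagnosis of malaria elsewhere". The exclusion list that follows removes "Patients referred on for diagnosis in the private sector".

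The primary outcome (section 2.6.1) is "Proportion of patients (in)correctly treated by CHWs". Correct treatment includes "No antimalarial for PCR confirmed negative diagnosis" and "Treatment of PCR confirmed Pv with CQ (regardless of accompaniment with SP or addition of primaquine".

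In section 2.5.1, Arm 1 is based on "existing clinical diagnosis, pre-referral treatment and referral to a clinic in areas where RDTs have not been deployed at CHW level". Arm 2 has "CHWs using RDTs to provide parasitological diagnosis to diagnose, treat and/or refer patients".

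On sampling, section 2.9.2 states: "If the RDT is not used (i.e. in the non-intervention group) then the filter paper will be collected during the consultation".

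Section 2.8.1 plans for 10% correctly treated in Arm 1 against 50% in Arm 2, and for antimalarial use in malaria-negative patients of 90% against 50%.

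**The concern.** An exclusion criterion should rest on something settled before the intervention can act. This one rests on the CHW's choice of action, made after the clinic's allocation and within the consultation that the primary outcome scores. Referral for a test is also a behaviour that giving CHWs an RDT is meant to replace, so the two arms are unlikely to lose the same share or the same kind of patient.

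The primary outcome does not need the exclusion. It concerns treatment by the CHW, and the blood spot is taken during the consultation, so whatever happens later in the private sector does not enter it.

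If the excluded patients were treated correctly more or less often than those kept, the Phase I comparison is distorted. The same applies to the secondary outcome on antimalarials in malaria-negative patients. A later analysis plan cannot repair this, because a patient who is never enrolled has no consent, blood spot or PCR result. In Phase II both arms have RDTs, so the problem should be smaller there.

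**Working it through.** **Plan's figure.** Section 2.8.1: 50% − 10% = 40 points, as stated.

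**Inputs that the protocol does not give (assumed, shown over a range).**
- f: share of otherwise eligible Arm 1 patients who are referred privately.
- c: share of those patients whom the CHW treated correctly.
- The 10% is taken as the rate among Arm 1 patients who are kept, and Arm 2 is held at 50% with no loss.

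**Formula.** Arm 1 with the excluded patients restored = (1 − f) × 0.10 + f × c. The bias in the difference is therefore f × (c − 0.10); a positive value means the effect is inflated.

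| f | c | Arm 1 restored | Difference | Bias in points |
|---|---|---|---|---|
| 1% | 0.90 | 0.099 + 0.009 = 10.8% | 39.2 | +0.8 |
| 5% | 0 | 0.095 + 0 = 9.5% | 40.5 | −0.5 |
| 5% | 0.10 | 0.095 + 0.005 = 10.0% | 40.0 | 0 |
| 5% | 0.90 | 0.095 + 0.045 = 14.0% | 36.0 | +4.0 |
| 10% | 0 | 0.090 + 0 = 9.0% | 41.0 | −1.0 |
| 10% | 0.90 | 0.090 + 0.090 = 18.0% | 32.0 | +8.0 |

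At f = 1% and c = 0.95 the inflation is 0.01 × 0.85 = 0.85 point.

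**What c might be.** Assume 90% of those referred are PCR-negative, and let q be the share given an antimalarial before referral.
- q = 0: c = 0.90.
- q = 0.90, the section 2.8.1 figure for malaria-negative Arm 1 patients: c = 0.90 × 0.10 = 0.09 from the negatives alone. If every positive is vivax and 90% of them get CQ, c = 0.09 + 0.10 × 0.90 = 0.18. At f = 5% the bias is 0.05 × (0.09 − 0.10) = −0.05 point to 0.05 × (0.18 − 0.10) = +0.4 point.
- q = 1: c lies between 0 and 0.10, so the effect is unchanged or slightly understated.

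**If Arm 2 also loses patients.** Take half the Arm 1 rate (2.5%), with f = 5%.
- c = 0.90: Arm 2 restored = 0.975 × 0.50 + 0.025 × 0.90 = 51.0%; difference 51.0 − 14.0 = 37.0; inflation 3.0 points.
- c = 0: Arm 2 restored = 48.75%; difference 48.75 − 9.5 = 39.25; inflation 0.75 point.

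The sign therefore also depends on the loss in Arm 2. The turning point at c = 0.10 holds only if that loss is nil.

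**The case against.** A reader might infer that the rule deletes correctly treated controls and so inflates the effect. The documents do not support that as a statement of fact. It requires Arm 1 CHWs to refer privately without giving an antimalarial. The protocol describes Arm 1 care as including treatment before referral, and expects 90% of malaria-negative Arm 1 patients to receive an antimalarial. Applied to the privately referred, that figure makes the bias close to nil. This objection stands against any fixed direction.

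It does not remove the risk. The footnote to section 2.8.1 says the starred estimates, the 90% among them, come from the earlier trial in the clinics and that no regional estimate exists at CHW level. The 90% also averages over all malaria-negative patients, not those sent away for a test. The inclusion criterion lists prescribing, wanting a test and referring as alternatives, so the protocol foresees referral without a prescription.

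A reader might also see a flat contradiction between inclusion and exclusion. The word *elsewhere* can cover referral to a study clinic, which is the Arm 1 pathway, and section 2.10.3 says all clinics have parasitological diagnosis. The exclusion can thus be read as a carve-out. The overlap needs clarifying but is not a strict contradiction.

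Nor do the documents show that the loss falls almost only in Arm 1. No private-referral rate is given for either arm, Arm 2 CHWs may also refer, and section 1.2 reports invalid and misapplied RDTs in earlier CHW use. A difference between arms is a reasonable inference from the arm definitions, not a documented fact.

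Finally, the exclusion has a rationale for outcomes that use clinic data, since private patients leave that pathway. Section 2.4 also asks about CHW referral practice and compares the arms. That work is done in a subgroup and cannot correct the primary outcome.

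**Conclusion.** The point holds as a selection-bias risk of unknown direction. The exclusion is conditioned on a post-randomisation CHW action, is likely to operate differently by arm in Phase I, and serves no purpose for the primary outcome.

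With no loss in Arm 2 and 10% correct among the Arm 1 patients kept, the risk is lopsided: c can fall only 10 points below that rate but can rise far above it. Inflation can therefore be several points, while understatement is limited to f × 10 points. If private referral is rare, the effect is negligible. The protocol gives neither f nor c, so these figures are illustrations over assumed ranges and not estimates of the bias. The change is worth making whichever way the bias runs, because the lost information cannot be recovered.

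**What to change.** Drop this exclusion for the CHW-level population and the primary outcome, and clarify what *elsewhere* covers in the inclusion criterion. Enrol these patients, take the blood spot in the consultation, and score the CHW's own treatment against PCR. Make sure the CHW form records private referral as an action; section 2.7.2 says the form captures the action taken, but the form itself (Annex 4) is not visible here, so it may already do so. Omit these patients only from outcomes that need a study-clinic visit, and report their number by arm.

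The cost is one deleted criterion, possibly one form category, and a few more patients enrolled and sampled. Their later private treatment stays unknown, but the primary outcome does not use it. Care of the patient is unchanged.
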